### Data monitoring

The data monitoring committee, composed of statisticians, representatives from the ethics committee, and principal investigators from each center, will be responsible for data monitoring. The members of the DMC are independent of the sponsors. Written reports on trial progress will be submitted to the committee quarterly. Cases of unexpected scenarios and adverse events will be discussed at committee meetings.

### Statistical analysis

Statistical analyses will be performed by an independent statistician using the SPSS 19.0 statistical software. The measurement data of normal distribution will be presented as mean ± standard deviation. Independent sample *T* test or rank-sum test will be used for comparison between the groups, and multiple linear regression analysis will be used to test the relationship between the dosage of remimazolam and TBL, TBA, ALB, AST, and ALT.

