#### Eligibility

The study takes place at three centers: the Department of Anesthesiology, Shidong Hospital of Shanghai, University of Shanghai for Science and Technology; Department of Anesthesiology, Eastern Hepatobiliary Surgery Hospital, Second Military Medical University; and Department of Anesthesiology, Chongqing University Cancer Hospital beginning March 2021 to March 2022. Eligible patients for participation in this clinical trial are 32 patients with obstructive jaundice (serum TBL > 17.1 μmol/L) secondary to neoplasm of the bile duct or the head of the pancreas and 32 non-jaundiced patient controls with chronic cholecystitisor intrahepatic bile duct stones. All patients enrolled in this clinical trial are aged 18 to 75 years, American Society of Anesthesiologists (ASA) grades II to III, and given written informed consent, who are scheduled to undertake surgery.

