### Allocation and allocation concealment

Patients are allocated to the obstructive jaundice group or the control group based on the TBL values after they sign the informed consent form. Because obstructive jaundice is easy to distinguish from the appearance of skin color, it is difficult to double-blind. However, the anesthesiologist assistant is blind to the grouping or induction method but only records the data through a local area network (LAN) in the next room.

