### Primary objective

#### Definition of primary endpoint

The primary endpoint of the study—reflecting the change of sensitivity of remimazolam in patients with obstructive jaundice—is remimazolam requirement with BIS of 50 as the endpoint.

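### The groups are not randomised, but the only group comparison is unadjusted, so differences in age, sex or centre may be read as an effect of jaundice

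*Protocol article*

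**What the plan says.** Under Allocation and allocation concealment, the protocol article states: "Patients are allocated to the obstructive jaundice group or the control group based on the TBL values". Under Eligibility, the jaundice in the case group is "secondary to neoplasm of the bile duct or the head of the pancreas", and the comparison group is "32 non-jaundiced patient controls with chronic cholecystitisor intrahepatic bile duct stones". Both groups are "aged 18 to 75 years, American Society of Anesthesiologists (ASA) grades II to III". On sites, the same section says: "The study takes place at three centers". No matching, stratification or balancing of the groups is described.

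The primary endpoint "is remimazolam requirement with BIS of 50 as the endpoint". Under Statistical analysis, an independent-samples t-"test or rank-sum test will be used for comparison between the groups". The same sentence adds a multiple linear regression of dose on total bilirubin, bile acid, albumin, AST and ALT. Age, sex, ASA class, centre and underlying diagnosis are not in that list, and the regression is not described as an adjusted comparison of the groups.

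The end of the Discussion gives the aim in causal terms: to show that obstructive jaundice changes the pharmacodynamics of remimazolam. The Abstract draws a dosing implication from this.

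**The concern.** In a randomised trial, a raw two-sample test estimates the effect of treatment because the groups are alike in expectation. Here the groups are two patient populations, so the test estimates the total difference between them, whatever its source. Any factor that both differs between the populations and affects the dose needed to reach the BIS endpoint contributes to that difference.

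The planned regression does not close the gap. Total bilirubin defines the groups, and the other terms are further liver and bile markers. With age, sex and centre left out, any confounding by them carries over into the bilirubin coefficient as well.

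The primary conclusion is at stake. The planned difference is only 0.03 mg/kg, so a modest imbalance could make up a sizeable part of it. An imbalance in the other direction could hide a true difference.

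**Working it through.** **The plan's own figure.** The section on the number of patients gives means of 0.13 and 0.16 mg/kg, SD 0.04 in each group, α = 0.05 and power 0.8.
- Effect size = (0.16 − 0.13)/0.04 = 0.75.
- n = 15.7/0.75² + 1 = 28.9, so 29 per group, as stated.
- Noncentral-t power at 29 per group, two-sided 5%, is 80.1%.

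The calculation is sound, but it attributes the whole 0.03 mg/kg to jaundice.

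**Spurious difference without adjustment.** The document gives neither the imbalance in any covariate nor its relation to dose, so both are assumptions here:
- D, the between-group difference in one covariate in within-group SDs: 0.5 to 1.0.
- ρ, its within-group correlation with dose: 0.2 to 0.5.

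Spurious difference = ρ × D × 0.04 mg/kg. The false-positive rate is the rejection probability of the two-sided t-test with 56 degrees of freedom and noncentrality ρD × √(29/2), with no true effect of jaundice.

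| D | ρ | Spurious difference (mg/kg) | Share of 0.03 | False-positive rate |
|---|---|---|---|---|
| 0.5 | 0.2 | 0.004 | 13% | 6.6% |
| 0.5 | 0.3 | 0.006 | 20% | 8.7% |
| 0.75 | 0.4 | 0.012 | 40% | 20.2% |
| 1.0 | 0.5 | 0.020 | 67% | 46.5% |

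The first and last rows are the ends of the range.

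**Bias in the other direction.** If the true difference is 0.03 and confounding works against it by 0.010, the expected difference is 0.020 and power is 46.5%. If confounding works against it by 0.020, the expected difference is 0.010 and power is 15.5%.

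**Power of the adjusted comparison at 29 per group.** Let R²g be the share of group membership explained by the covariates and R²y the share of within-group outcome variance they explain. The effective effect size is 0.75 × √(1 − R²g)/√(1 − R²y).
- R²g = 0.2: power is 0.71 with R²y = 0, 0.75 with 0.1 and 0.80 with 0.2.
- R²g = 0.4: power is 0.59 to 0.68 for R²y from 0 to 0.2.
- R²g = 0.5: power is 0.51 to 0.60 over the same range.

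For a single covariate, R²g = (D²/4)/(1 + D²/4), so D = 1.0 corresponds to 0.25/1.25 = 0.2. Over the D and ρ ranges assumed above, adjusted power runs from 73% to 88%.

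**The case against.** The strongest reply is that the size of the problem is unknown. The document reports no age, sex or centre distribution by group and no effect of any of these on dose. The design also restricts some variation:
- the exclusion criteria remove patients far from ideal weight, with cardiac, pulmonary, renal, metabolic or psychiatric disease, or on analgesic or neuromodulating drugs;
- dose is expressed per kilogram;
- infusion rate, pump, sensor, room temperature and endpoint are fixed;
- the assistant who judges the endpoint does not know the group.

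This stands as a limit on certainty. Restriction and standardisation narrow confounding, but they do not balance age, sex or centre.

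It could also be said that covariates belong in a separate analysis plan. That would answer a silence, but this article states both the group test and the regression terms.

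Several stronger readings are tempting and are not supported:
- **The bias favours the hypothesis.** A reader might infer that cancer patients are older or frailer and so need less drug. Nothing in the document establishes this; the bias could go either way.
- **The false-positive rate could reach 80%.** That needs confounding to produce the entire 0.03 mg/kg, which is an extreme case.
- **Naming two tests inflates the error.** Mean and SD are tied to normally distributed data, so the usual reading is a t-test if normal and a rank-sum test otherwise. Even taking the smaller p-value of the two gave 5.4% in simulation.
- **Adjustment would justify the causal claim.** It would not. Malignant against benign disease coincides with group by design, and no covariate can separate it from jaundice.

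**Conclusion.** The point holds as a risk that the stated analysis leaves unprotected, not as a demonstrated bias. The groups differ by construction, the only comparison between them is unadjusted, and the one regression omits age, sex and centre. A difference in any of these may therefore be reported as an effect of jaundice.

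Under the assumed ranges for D and ρ, the spurious difference is 0.004 to 0.020 mg/kg and the false-positive rate about 7% to 47% at 29 per group. These figures rest on the plan's SD of 0.04, on one covariate acting linearly, and on imbalances and correlations that the document does not supply. They show how sensitive the result is; they do not predict it.

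**What to change.** In Statistical analysis, name one primary analysis: a linear model of remimazolam requirement on group, age, sex and centre, reporting the adjusted group difference with its 95% confidence interval. Fix it before outcome data are examined by group. Keep the raw t-test or rank-sum test as supportive. Add ASA class only in a sensitivity analysis, because it may partly reflect the jaundice itself and adjusting for it could remove real effect.

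Reword the aim and the planned conclusion as an association between obstructive jaundice and remimazolam requirement, and state that malignant against benign disease cannot be separated from it.

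**Cost.** This is a change of wording and needs no new design. Age is needed for eligibility and centre is known. Sex is not itemised under Data collection, which mentions only general information, so confirm that it is on the case report form. With 58 evaluable patients and six coefficients (intercept, group, age, sex, two for centre), 58 − 6 = 52 residual degrees of freedom remain.

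The real downside is power. The stated 80% applies to the unadjusted test and should be reworded: about 0.71 to 0.80 if the covariates explain 20% of group membership and 0 to 20% of the outcome, and lower if centre and group are strongly linked. A table of group by centre would show how strong that link is.

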## Discussion

Obstructive jaundice may result in hepatic cell damage and hepatosis through various mechanisms [10]. Alanine aminotransferase, aspartate aminotransferase, and alkaline phosphatase increased in obstructive jaundice patients [8, 11]. The drug-metabolizing enzyme systems may be impaired in patients with obstructive jaundice. Plasma clearance of drugs such as dexmedetomidine and rocuronium, which are metabolized and excreted by the liver, is decreased significantly in patients with obstructive jaundice. Furthermore, cardiovascular abnormalities have been well known to occur in obstructive jaundice patients for many years [12–14]. It was reported that internal biliary drainage produces an improvement in hemodynamics [15].

Remimazolam could be suitable for anesthesia of patients with obstructive jaundice, because remimazolam is not biotransformed in the liver. Schüttler et al. reported that remimazolam has a high clearance (1.15 ± 0.12 L/min), a small steady-state volume of distribution (35.4 ± 4.2 L), and a short terminal half-life (70 ± 10 min). The simulated context-sensitive halftime after an infusion of 4 h was 6.8 ± 2.4 min [16]. It was reported that remimazolam, which did not accumulate after prolonged infusion, could be used for the maintenance of general anesthesia in many nations [4, 17]. Furthermore, remimazolam was characterized by moderate hemodynamic side effects [16]. A multicenter, randomized, double-blind, parallel-group trial demonstrated remimazolam’s safety and efficacy in vulnerable patients (ASA class III) undergoing elective general surgery [18]. All these profiles of remimazolam determine its position in anesthesia for patients with obstructive jaundice, in which patients the duration of the operation is often relatively long and the hemodynamics is relatively unstable.

Hyperbilirubinemia has been well-described to have toxic effects on the brain. Histologic evidence of neurologic damage in the brain, such as atrophy and pyknosis of nerve cells, ghost cells, and neuronophagia, was observed in a well-designed canine model of cholestasis secondary to bile duct resection. Furthermore, neurologic damage is more widespread as the duration of hyperbilirubinemia is prolonged [19]. It has been reported that interaction of unconjugated bilirubin with synaptosomal membrane vesicles results in oxidative injury, calcium intrusion, and loss of membrane asymmetry and functionality, thus potentially contributing to the pathogenesis of encephalopathy by hyperbilirubinemia [20]. Acute hyperbilirubinemia results in presynaptic neurodegeneration at a central glutamatergic synapse [21]. Unconjugated bilirubin could also impair the release and uptake of the neurotransmitter glutamate, indicating possible excitotoxic damage [22, 23]. It has been reported that altered neurotransmission could occur in the brains of cholestatic patients. Some evidence suggests that fatigue and pruritus accompanying with cholestasis may be the consequences of a central mechanism, increased opioidergic neurotransmission [24, 25], and defective serotoninergic neurotransmission [26–28]. Consequently, all these changes in patients with obstructive jaundice may, at least in part, induce the increased sensitivity to anesthetics and the reduction of anesthetic requirements.

Our previous study demonstrates that the MACawake of desflurane was significantly decreased in obstructive jaundice patients compared with non-jaundiced controls; furthermore, there is a highly inverse relation between the MACawake of desflurane and the concentration of serum total bilirubin [29]. We also demonstrated that patients with obstructive jaundice had an increased sensitivity to isoflurane, more bradycardia and hypotension during anesthesia induction and maintenance, and a prolonged recovery time compared with non-jaundiced patients [30].

In our other research, it was shown that the etomidate requirement was significantly decreased in patients with obstructive jaundice, and there was a significant negative correlation between serum total bilirubin and etomidate requirement [8]. Etomidate is a pure hypnotic GABA agonist [31–33]. Shi et al. demonstrated that bilirubin potentiates inhibitory synaptic transmission in the lateral superior olive neurons of rats, and the potentiation of depolarizing GABA/glycinergic transmission by bilirubin could underlie bilirubin excitotoxicity [34, 35].

It just so happens that the remimazolam we are discussing is also a high-affinity and selective ligand for the benzodiazepine site on the GABAA receptor. Moreover, remimazolam does not show selectivity between GABAA receptor subtypes [5]. In other words, remimazolam and etomidate have the same mechanism of action when exerting an anesthetic effect. Patients with obstructive jaundice are more sensitive to etomidate [8], which suggests that patients with obstructive jaundice may also be more sensitive to remimazolam.

In conclusion, the toxic effects of hyperbilirubinemia on the central nervous system, such as histologic evidence of neurologic damage, altered neurotransmission in the brain, presynaptic neurodegeneration at the central glutamatergic synapses, and impairment of the release and uptake of the neurotransmitter glutamate, may induce the increased sensitivity to anesthetics and the reduction of anesthetic requirements.

The aim of our trial is to show that obstructive jaundice affects the pharmacodynamics of remimazolam, and the sensitivity of remimazolam increases among icteric patients; thereby, anesthesiologists caring for patients with obstructive jaundice should be alert to the interaction of bilirubin and remimazolam sensitivity.

### Trial status

The first patient was included on 1 March 2021. We expect to finalize the study in March 2022.

## Data Availability

Not applicable.
